#### Procedure

*In the first phase*, hospitals will be randomized and groups of five or six participants will be organized. Randomization will be collective between the hospitals and not between patients. The local catchment areas of the 12 psychiatric hospitals are sufficiently distant from each other to avoid a bias of contamination between individuals of the same hospital. The trial will be conducted in the open because it is not possible to assess a person’s oral health without the person and the operator knowing. Cluster randomization is recommended by the “la Haute Autorité de Santé” (HAS) in France for evaluation trials of interventions to improve practices.

*In the second phase*, patients able to participate in the study will be screened in each local catchment area. Consenting participants will be contacted to arrange an oral health assessment. Evaluations will be conducted at the outpatient unit or at the hospitals where the patients are followed. Prior to arriving in their TEPOH group, they will be asked to complete a battery of psychological and OHRQoL questionnaires. Participants’ socio-economic status (SES) will also be collected.

*In the third phase*, participants will undergo a battery of tests to assess their oral health disorders using clinical and radiological examinations. At the end of this step, the TEPOH will be performed or not depending on the cluster to which the PWS belongs.

Before the start of the TEPOH, the teams of caregivers for the patients will be invited to participate in a focus group interview to assess their knowledge of oral health and their practices in the management in OHrQOL with PWS.

*The fourth phase* will consist of an evaluation at 3 months, 6 months and at 1 year after the initiation of TEPOH. All participants (patients and caregivers) will be asked to complete the same battery of tests they completed at baseline except for radiological examinations and SES.

The interviews for the OHRQoL will be managed to ensure that participants in the two groups (control vs TEPOH group) do not interact with each other.

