### Sample

#### Eligibility

Table 1 summarizes the criteria used to determine the eligibility of participants. A potential participant must have been diagnosed with schizophrenia as defined in the Diagnostic and Statistical Manual of Mental Disorders-Fifth edition (DSM-5) [65] and be receiving in- or outpatient care in one of the hospitals taking part in the study. Potential participants, over 18 years of age, can be of either sex. Schizophrenia is a severe mental disorder characterized by a set of different symptoms varying in intensity [3]. Persons not stabilized from a psychiatric viewpoint will be excluded. Persons will be excluded if hospitalized under stress or the person does not perceive the significance of the study or is not motivated to take care of their oral health. We will exclude people with severe somatic disorders regarding the aims of the study so as not to generate management problems of health care. Finally, we will exclude edentulous persons, because the absence of teeth is a limitation of our TEPOH for our end-point (periodontal disease) and temporarily for persons who have not updated their social rights to cover the cost of medical and dental care. In France, medical and dental care costs are covered by national health insurance and complementary health insurance or by universal health insurance (CMU) depending on the level of income. For people with low incomes, below 7771€ per year, CMU is free [66]. Indeed, as the aim of the program is to motivate participants to improve their oral health, if a participant does not have financial resources to access the health care system, the programme will be counterproductive. PWS have less access to dental care because of its cost. This problem must be solved before their inclusion in the study.

**Table 1 Tab1:** Inclusion and exclusion criteria

Inclusion criteria	Exclusion criteria
Persons who have provided consent	Persons not covered by national health insurance
Persons of either sex over 18 years of age	Persons not stabilized from a psychiatric viewpoint or persons in an acute psychiatric episode
Persons with diagnosis of schizophrenia as defined in the Diagnostic and Statistical Manual of Mental Disorders-Fifth edition (DSM-5)	Pregnant or breast-feeding women Edentulous persons Persons hospitalized under stress

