#### Recruitment procedures

In 1960, France opted for mental health care based on the definition of local catchment areas. The country was divided into sectors of approximately 70,000 inhabitants [67]. Each sector is run by a reference hospital and a multidisciplinary team intended to provide preventive, as well as curative and rehabilitative care for all those within the catchment area who need it. Care is provided as close to home as possible. Patients can only have ongoing contact with the psychiatric sector’s outpatient unit and live in the community or can be hospitalized depending on severity their mental disorders [67]. The 12 hospitals that will take part in the study cover 42 psychiatric sectors. There are potentially 2,940,000 inhabitants and about 29,400 PWS for recruitment in the study. The local catchment areas of the 12 psychiatric hospitals are sufficiently distant from each other. The two closest hospitals are 60 kms apart, and the farthest are 600 kms apart. The 12 hospitals participating in the study are spread over the eastern half of France.

To maximize recruitment, co-investigators will provide information on the study in the different hospitals. They will inform potential participants about the study by means of the internal communication system for caregivers of the institution (e-mail or newsletter) and via the distribution of flyers informing PWS about the study. Those who express an interest will be given details of the study and screened for their eligibility by the study team of the co-investigator. All participants (caregivers and PWS) will be aware that the study relates to an assessment of the effectiveness of TEPOH and the exact nature of the research project (i.e., the existence of the intervention and control groups and the comparison of outcomes between them). Upon debriefing at the end of the study, the PWS who were in the no-TEPOH group could benefit from TEPOH.

Participants may withdraw from the trial either at their own request or at the discretion of the Investigator (acute psychiatric disorders). Participants will be made aware that withdrawal will not affect their future care. All participants (PWS and caregivers) will be made aware (via the information sheet and consent forms) that should they withdraw, the data collected to date cannot be erased and may still be used in the final analysis.

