## Trial status

The preliminary phase of the study is completed and data collection for patients is closed. We will proceed with randomization of the clusters and will include the first patients in the study during July, 2016.

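### Hospitals are randomised before patients are screened and assessed, in an open trial with no described concealment and a subjective motivation exclusion, so enrolment and baseline self-report can differ by arm

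*Protocol article*

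**What the plan says.** The Procedure section of the protocol article sets out the order. In the first phase, "hospitals will be randomized and groups of five or six participants will be organized". In the second phase, "patients able to participate in the study will be screened in each local catchment area"; those who consent are booked for assessment and complete the baseline questionnaires. The third phase is the baseline oral examination, after which TEPOH is or is not delivered according to the cluster. Trial status gives the same order: "We will proceed with randomization of the clusters and will include the first patients in the study during July, 2016".

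The Procedure section adds "Randomization will be collective between the hospitals and not between patients" and "The trial will be conducted in the open". Under Recruitment procedures, people who respond to the publicity are "screened for their eligibility by the study team of the co-investigator". The Eligibility text excludes a person who "does not perceive the significance of the study or is not motivated to take care of their oral health". Table 1, which is presented as the summary of the criteria, does not list that exclusion.

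The two arms ask different things of a patient. TEPOH takes five sessions of 90 minutes (7.5 hours), whereas control participants are only examined, at baseline and at 3, 6 and 12 months.

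**The concern.** Randomising hospitals balances hospitals in expectation. It does not protect the choice of which patients enter once a hospital's arm is fixed. If recruiters or patients know the arm, a criterion that rests on judgement can be read more strictly where the patient must attend a course of sessions. Patients can also select themselves more strongly there.

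Motivation for oral care is plausibly related to the primary endpoint. The Background lists dental visits and smoking among the predictors of periodontal disease and describes the disease as partly behavioural. Better-motivated entrants in the TEPOH hospitals would lower the proportion with CPI≥3 there even if the programme did nothing.

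Baseline self-report (oral-health quality of life, schizophrenia quality of life, depression, brushing habits) is also collected after randomisation, so the answers may be coloured by the expected arm.

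**Working it through.** **1. Order of events**

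| Step | Where stated | Before or after hospital randomisation |
|---|---|---|
| Hospitals randomised | Procedure, first phase; Trial status | – |
| Screening and consent | Procedure, second phase | After |
| Baseline questionnaires | Procedure, second phase | After |
| Baseline oral examination | Procedure, third phase | After |
| TEPOH starts, or not | Procedure, end of third phase | After |

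No section describes concealing the arm from recruiters or patients, identifying patients before randomisation, or independent screening.

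**2. The planned effect, as a yardstick**

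The Sample/randomization section gives 40% with CPI≥3, a 20% reduction, CV 0.37, ICC 0.01, 5% type-I and 20% type-II error, and 202 patients. Take 0.40 against 0.20, a two-sided test and no continuity correction:

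- n per arm = [1.96·√(2·0.30·0.70) + 0.8416·√(0.40·0.60 + 0.20·0.80)]² / 0.20² = 81.2, rounded up to 82, or 164 in total.
- Design effect, reading CV as variation in cluster size, with m = 230/12 = 19.17: 1 + [(1 + 0.37²)·19.17 − 1]·0.01 = 1.208.
- 164 × 1.208 = 198, close to the stated 202.

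A relative reduction (0.40 to 0.32) needs 926 or more under every variant tried. The planned effect is therefore best read as 20 percentage points.

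**3. Illustration of selective enrolment**

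The inputs are assumed and are not in the document: 30% of otherwise eligible patients are poorly motivated, and 60% of these have CPI≥3. For 40% overall, the rest must have (0.40 − 0.30·0.60)/0.70 = 0.22/0.70 = 31.4%.

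If a hospital excludes a fraction f of the poorly motivated, the prevalence among those enrolled is

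p(f) = [0.22 + 0.30(1 − f)·0.60] / [0.70 + 0.30(1 − f)].

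- f = 0: 0.40/1.00 = 40.0%
- f = 1/3: (0.22 + 0.12)/0.90 = 37.8%
- f = 2/3: (0.22 + 0.06)/0.80 = 35.0%
- f = 1: 0.22/0.70 = 31.4%

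| Excluded in TEPOH | Excluded in control | Spurious difference |
|---|---|---|
| Any fraction | The same fraction | 0 points |
| 2/3 | 1/3 | 37.8 − 35.0 = 2.8 points |
| 2/3 | None | 40.0 − 35.0 = 5.0 points |
| All | None | 40.0 − 31.4 = 8.6 points |

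**4. Effect on a 5% test when TEPOH does nothing**

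Assume an unadjusted two-sided comparison of proportions with a normal reference. For an imbalance d, SE = √{[p₁(1 − p₁) + p₂(1 − p₂)]/(N/2) × design effect}, and the rejection probability is 1 − Φ(1.96 − d/SE) + Φ(−1.96 − d/SE). The design effect is 1.181 at N = 202 (m = 202/12) and 1.208 at N = 230.

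| Imbalance | N = 202 | N = 230 |
|---|---|---|
| 0 points | 5% | 5% |
| 5 points (40% v 35%) | 10% | 11% |
| 10 points (40% v 30%) | 28% | 31% |

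The 10-point row lies slightly beyond the worst case in step 3.

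**The case against.** **The exclusion is a rule for the whole trial.** A reader might infer that control hospitals apply no motivation filter. The Eligibility text contradicts this: the criterion applies in every hospital, and recruitment follows one route. Applied equally, it produces no bias. What stands is that one subjective rule may be applied, or met with self-selection, unequally. The 5- and 9-point figures assume control hospitals exclude nobody, so they are not estimates.

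**Knowledge of the arm is inferred.** A reader might take it as stated that recruiters and patients know the arm before consent. The document does not say so. The reason it gives for openness concerns the oral assessment. Participants are told that two groups exist, but the document does not say they are told which is theirs. A statistics unit performs the randomisation, and the full protocol may settle when the result is disclosed. This limits the confidence but does not remove the point, because the article fixes the order and describes an open trial without concealment.

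**Baseline CPI precedes TEPOH.** An imbalance would be visible and could be adjusted for. That is right in part, and the figures above are unadjusted. Adjustment does not reach differences in unmeasured motivation, which may also affect attendance and response.

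**The primary endpoint is a probe measurement by calibrated examiners.** Arm-coloured self-report therefore touches secondary measures only. Calibration (kappa 0.9) bears on measurement, however, and not on who is enrolled.

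**Control participants may receive TEPOH afterwards.** This narrows the difference in incentive but leaves the difference in immediate burden.

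**Other wording could suggest that patients come first.** The Abstract and Methods/design speak of patients allocated 1:1, and Trial status says patient data collection is closed. The Procedure section rules out randomisation between patients, and Trial status itself places the first inclusions after randomisation. Neither remark shows that patients were identified beforehand.

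**Conclusion.** The point holds as a risk created by the stated order. Hospitals are randomised first; local teams then screen with a subjective criterion in an open trial, and no concealment is described. Enrolment and baseline self-report can therefore differ by arm.

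Its size cannot be derived from the document. Under the assumed inputs the spurious difference is 0 points with equal screening, about 5 points with two thirds against none, and about 9 points in the extreme case, set against a planned effect read as 20 points. These are differences before adjustment; baseline CPI would remove part of them. The direction favouring TEPOH is plausible but not demonstrated. The document does not support a claim that bias will occur, or that it will reach nearly half the planned effect.

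The change is nevertheless worth making: Trial status shows that the hospitals had not yet been randomised, and the flaw is hard to repair once enrolment has begun.

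**What to change.** Reorder the phases. Each hospital screens, obtains consent, and completes the baseline questionnaires and CPI for its patients (about 19, from 230/12). Only then does the statistics unit disclose that hospital's allocation. Form the groups of five or six afterwards.

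At minimum, lock each hospital's list of eligible and consented patients before disclosure. This protects enrolment, but not baseline answers collected later.

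State that the motivation criterion is to be applied identically in both arms, and reconcile the Eligibility text with Table 1, which omits it.

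Stratification uses only hospital-level factors (location and activity), so it is unaffected. The cost is delay: early recruits wait until their hospital's list closes, some baselines age, and a few patients may withdraw or become psychiatrically unstable before the start. The Limitations section already foresees non-cooperation and loss to follow-up in this population, so the waiting period should be kept short.

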#### Interventions

All participants at the twelve sites will be interviewed and clinically examined by the co-investigators.

Demographic and medical variables were extracted from institutional medical records: diabetic or not, prescribed drugs at the time of the examination, duration of mental illness. Other variables, namely the level of education, residential area, smoking habits, tooth brushing frequency and last dental visit, were collected directly by questioning the patient. Each participant will be asked to complete the French version of global oral health assessment index (GOHAI) [68], the schizophrenia quality of life questionnaire (S-QOL) [69], the Beck Depression Inventory-(BDI-II) [70], the stability status of symptom severity scale (PANSS) [71] and to answer other questions relating to their SES, health status (duration of mental illness), dental attendance and oral behaviour (smoking habits, tooth brushing frequency).

In a second time, each person will undergo a clinical oral examination in the dental surgery of the hospitals participating in the study. Pre-packaged and disposable instruments—dental mirrors, tweezers, 0.5 mm ball-ended CPITN probes (3.5–5.5 mm)—will be used and cotton rolls will be used to remove plaque. Caries will be assessed at the dentinal (D3) level using the DMFT index [72]. Dental plaque and calculus will be evaluated using the simplified oral hygiene index (OHI-S) [73] and periodontal disease by the community periodontal index of treatment needs (CPITN) [26].

This investigation will require 1 h for each participant. At the end of this evaluation, the TEPOH could start, as described previously, in all clusters selected for the study.

The mental health of PWS will be closely monitored by their care teams, and care co-investigators will be asked to inform the trial team of any adverse event that either the care co-ordinator or patient notices. The trial team will determine the seriousness and causality in conjunction with treating medical practitioners. Serious adverse events are divided into two categories, those that seem likely to be independent of TEPOH and those connected with TEPOH. All adverse events will be recorded and closely monitored until resolution, stabilization, or until it has been shown by the data monitoring committee that involvement in the trial is not the cause. All treatment-related serious adverse events will be recorded and reported to the Research Ethics Committee (REC) as part of the annual reports. Unexpected serious adverse events will be reported to the REC by the chief investigator, who will take appropriate medical action, which may include halting the trial and informing the sponsor of such action. Any participant who experiences an adverse event may be withdrawn from the study at the discretion of the investigator.

#### Control

Participants assigned to the control condition will be advised to maintain their existing lifestyles or take on new activities as they see fit. They will be examined only at the clinical evaluation at the start of the study and at 3, 6 and 12 months. For ethical reasons, if the program shows its effectiveness, it will be made available to all groups at the end of the study.

#### Outcomes

*Our primary end*-*point* will be the impact on periodontal disease. We have chosen periodontal index for our primary outcomes. Indeed, periodontal diseases are in relation with predictor in oral health (medical and dental condition, behavioural and SES) [29, 30].

The community periodontal index of treatment needs (CPITN) will be used to assess the periodontal status of the participants in the survey [26]. With the help of a World Health Organization periodontal probe, the depth of the periodontal pocket will be measured at six points on both the buccal (facial) and (lingual or palatal) surfaces of the index teeth. This measure will be used to score periodontal status and assess patients’ treatment needs. The initial sign of periodontal disease is bleeding of the gums. As it progresses, the gum retracts from the root surface of the tooth to form pockets. The deeper the pocket, the more severe the periodontal disease. The CPITN is a 5-point scale graduated as follows: no sign of periodontal disease (0), gingival bleeding after gentle probing (1), supragingival or subgingival calculus (2), pathological pockets 4–5 mm deep (3) and pathological pockets >5 mm deep (4).

*The secondary end point* will be impact on caries measured by the DMFT score [72]. Decay will be assessed using this standardized index to evaluate existing or past dental caries with scores ranging from 0 to 32. This examination will assess dental caries, dental restorations, fissure sealants, fixed prostheses, missing teeth and an additional category for traumatized incisors. High scores indicate worse dental health [72]. Root caries will not be assessed in this study.

*Other secondary evaluation criteria* will include a hygiene index. The debris index component of the simplified oral hygiene index (OHI-S) [73]. This tool will be used to measure the amount of debris. It will be scored on six tooth surfaces per participant.

For all of the dental examinations above, the dental specialists have been calibrated against the chief investigator, through repeated examinations of a separate pilot sample using similar indices, followed by meetings to discuss discrepancies and standardize procedures. Kappa scores of 0.9 for inter-rater agreement were achieved.

The following four tools will be used in this study: The OHRQoL from the French version of the self-assessment GOHAI scale [68]; schizophrenia quality of life from S-QoL [69]; The stability status of symptom severity from the PANSS scale [71] and depressive symptoms of schizophrenic persons from the Beck Depression Inventory scale [70].

Finally, a panoramic radiograph will be done if the patient does not have radiographs dating back less than 3 months. The dental panoramic film (orthopantomogram) is to detect periodontal disease, fractures, tumours and bone disorders from teeth and conditions that may affect the jaw and sinuses. A qualitative analysis of data collected during the TEPOH will make it possible to determine the evolution of representations, knowledge, attitudes and the practices of patients and professionals, and the ability of patients and professionals to assimilate an educational process.

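### Total DMFT, the caries secondary endpoint, gives no credit for treating existing decay; untreated decay should be compared between arms alongside it

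*Protocol article*

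**What the plan says.** The Outcomes section of the protocol article defines the secondary endpoint as "impact on caries measured by the DMFT score". It calls DMFT a standardized index used "to evaluate existing or past dental caries with scores ranging from 0 to 32", and adds: "High scores indicate worse dental health". The components are all recorded: "This examination will assess dental caries, dental restorations, fissure sealants, fixed prostheses, missing teeth". The Interventions section sets the threshold for decay: "Caries will be assessed at the dentinal (D3) level using the DMFT index". The Procedure section schedules follow-up at 3, 6 and 12 months after the programme starts, and the Control section gives the control arm the same examinations.

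Several sections make access to dental care part of how the programme should work. The Background lists regular dental visits among the things that matter for managing oral health. The Study process section gives one of the three workshops to making the dental surgery less frightening. The Eligibility section holds back people whose cover for dental costs is not in order, because the programme would work against its own aim if they could not obtain care.

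On hygiene, the Interventions section says that "cotton rolls will be used to remove plaque" and, two sentences later, that plaque and calculus are scored with OHI-S. The Outcomes section takes only the debris component of OHI-S as an outcome.

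**The concern.** The endpoint and the expected mechanism do not match. If the programme succeeds in getting participants to a dentist, its quickest effect on caries is that decayed teeth are treated. Total DMFT moves such a tooth from one component to another and leaves the sum unchanged. All that is left to detect is a lower rate of new lesions, within a year, after a programme lasting two months.

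What is at stake is interpretation. A trial in which the TEPOH arm had much of its decay treated, and the control arm had none treated, could report no difference on its caries endpoint. A reader would reasonably take that to mean the programme had no impact on caries.

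**Working it through.** The article gives no effect size, SD or power for DMFT, so there is no stated figure to reproduce. The check has three parts.

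**1. The identity.** DMFT = D + M + F, from the article's description of existing or past caries with restorations and missing teeth recorded. Illustrative changes for one patient:

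| Baseline and events | Change in D | Change in F | Change in M | Change in DMFT |
|---|---|---|---|---|
| 4 decayed, nothing done | 0 | 0 | 0 | 0 |
| 4 decayed, all filled | -4 | +4 | 0 | 0 |
| 4 decayed, all extracted | -4 | 0 | +4 | 0 |
| 4 decayed, all filled, 1 new untreated lesion | -3 | +4 | 0 | +1 |
| D5, M5, F5; 3 filled and 2 extracted | -5 | +3 | +2 | 0 (15 to 15) |

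The first three rows are clinically very different and have the same DMFT change. If the two arms have the same number of new lesions, the expected DMFT difference is 0 at any sample size, however much more decay is treated in one arm.

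**2. The signal that remains: new lesions.** Inputs from the Sample/randomization section are N = 202, CV = 0.37, ICC = 0.01 and 5% type-I error; there are 12 hospitals. The ICC was given for the periodontal endpoint, so using it for DMFT is an assumption. No loss to follow-up is allowed for.

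- Mean cluster size m = 202/12 = 16.83.
- Design effect = 1 + ((1 + CV²)m - 1) × ICC = 1 + (1.1369 × 16.83 - 1) × 0.01 = 1.18.
- Effective number per arm = 101/1.18, about 85.5.
- Power = Φ(δ/(SD × √(2/85.5)) - 1.96), where δ is the control increment times the proportion of new lesions prevented.

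The 12-month control increment (0.5 to 1.5 teeth) and its SD (1 to 2) are assumptions; the article gives neither.

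| New lesions prevented | Increment 0.5, SD 2 | Increment 1.0, SD 1.5 | Increment 1.5, SD 1 |
|---|---|---|---|
| 20% | 0.05 | 0.14 | 0.50 |
| 50% | 0.13 | 0.59 | 0.998 |
| 100% | 0.37 | 0.99 | 1.00 |

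The smallest difference detectable with 80% power is 2.80 × SD × √(2/85.5): 0.43 teeth at SD 1, 0.64 at SD 1.5 and 0.86 at SD 2. Using the 230 patients named in the Methods/design section changes little: the design effect is 1 + (1.1369 × 19.17 - 1) × 0.01 = 1.21, the effective number is 115/1.21, about 95, and at SD 1 the detectable difference is 2.80 × √(2/95) = 0.41.

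**3. The hygiene score.** In the Interventions section, one sentence lists mirrors, tweezers, probes and cotton rolls, including the removal of plaque. The following sentences name the indices by condition. No word places one step before or after another. Debris is what cotton rolls would remove, and the Outcomes section uses debris alone, so the order matters to that outcome; the text does not settle it.

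**The case against.** The strongest reply is that the trial compares arms. A cumulative index shows prevention as a smaller rise than in control, so DMFT can show a benefit. That stands. A reader might infer that DMFT is incapable of showing one; the table above contradicts this, since a large preventive effect would be detected under the more favourable assumptions.

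A reader might also infer that DMFT could move against TEPOH when it works, because more dental visits reveal more decay. The article does not support this. Both arms have the same scheduled study examinations, at the same D3 threshold, by calibrated examiners, so attending a dentist more often does not make the study examiner find more. In the fourth row of the first table, the +1 is a true new lesion that would count equally in either arm, and the four fillings contribute nothing. That is insensitivity, not reversal.

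It can also be said that separate analysis of D, M and F may sit in an analysis plan that is not shown. That is possible, and the absence of such an analysis is not the point. The point is what the article fixes: total DMFT as the measure of impact on caries. Finally, D3 alone has its own weakness, because extracting four decayed teeth would score -4, the same as restoring them. That stands and shapes the fix.

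On hygiene, a reader might infer from the sentence order that debris is scored on wiped teeth. The article lists materials and then indices, fixes no sequence, and reports that examiners met to standardize procedures. This is a matter of clarity only.

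**Conclusion.** The point holds for the caries endpoint. By the article's own definition, total DMFT is blind to treatment of existing decay: the change is exactly 0 per tooth filled or extracted, whatever the sample size. This follows from the index and needs no assumption. The endpoint therefore measures prevention only, and for modest prevention over 12 months it is weak: power of 0.05 to 0.50 for 20% fewer new lesions. Those power figures rest on the assumed increments and SDs, the borrowed ICC and complete follow-up.

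A null DMFT difference should not be read as no impact on caries. This concerns a secondary endpoint; the periodontal primary endpoint and the patient-reported scales are not affected. The order of plaque removal and debris scoring is a minor ambiguity and carries no weight in this conclusion.

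**What to change.** - Keep the DMFT increment, and label it as the measure of new caries.
- Add, as a caries outcome, the between-arm comparison of change from baseline in untreated dentinal decay (D at the D3 threshold).
- Always show it with the between-arm changes in F and M, so that decay removed by extraction is not read as the same benefit as decay restored.
- As a clarification, state in the Interventions section that OHI-S debris is scored before plaque is removed, with the same order at every visit and in both arms. Reconcile that section, which names plaque and calculus, with the Outcomes section, which uses debris only.

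The cost is small. D, M and F are already recorded to form DMFT, so no new data are needed. The downside is one more secondary comparison. The Trial status section places cluster randomization and first inclusions still ahead, so at that stage the change could be made before any trial data existed.
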